## Abstract

**Background:**

Palliative care interventions in the intensive care unit have been shown to improve communication and the quality of death and dying. However, few interventions have been implemented in safety-net hospitals (SNHs), which provide healthcare to low income and uninsured patients. The 3 Wishes Project (3WP) is a low-cost intervention that aims to enhance compassionate end-of-life (EOL) experiences by empowering the clinical team to elicit and fulfill small wishes for patients who are dying in the ICU.

**Objective:**

To implement and evaluate the 3WP in three SNHs in Los Angeles.

**Methods:**

We conduct a pragmatic cluster-randomized stepped wedge type 2 hybrid effectiveness-implementation study to implement and evaluate the effect of the 3WP (compared to usual care) on quality of EOL ICU care, bereaved families’ psychological symptoms, and clinician burnout. Prior to implementation, interviews with stakeholders from each hospital will refine the implementation strategy. Starting 6–10 months prior to 3WP implementation at each site and continuing throughout the study, we will survey bereaved families once 3 months after each patient’s death. Surveys will query: EOL care, anxiety, depression, and post-traumatic stress disorder (PTSD). Each SNH ICU starts the 3WP at a randomly assigned time that is staggered by 2 months. Nurses are surveyed on burnout before implementation, 6 months, and 12 months after 3WP implementation. Semi-structured interviews are conducted with 10–12 family members per SNH who received 3WP and 10–12 nurses per SNH a year after implementation. We will use the RE-AIM (Reach, Effectiveness, Adoption, Implementation, and Maintenance) framework to guide a mixed-methods evaluation of the 3WP implementation in SNHs.

**Conclusion:**

We hypothesize that it will be feasible to adapt and implement the 3WP in SNHs. We will evaluate how the 3WP improves EOL care in this setting and provide valuable insight regarding the adaptations necessary to tailor palliative care interventions for SNH ICUs.

**Trial registration:**

ClinicalTrials.gov NCT06277310.

## 1. Introduction

Palliative care interventions in the ICU have been shown to increase family satisfaction in the quality of death and dying [1], improve communication [2–4]. and decrease bereaved families’ psychological symptoms [5]. Compassionate end-of-life (EOL) care is foundational to medicine, but few palliative care interventions have been tested or implemented in safety-net hospitals (SNHs). SNHs are public hospitals that provide disproportionate amounts of healthcare to low-income and uninsured patients [6,7] and have less discretionary funds for innovative initiatives. Patients often present to SNHs with such advanced disease that it is often difficult to establish clinician-patient rapport prior to EOL conversations. A legacy of medical neglect and limited access to care can create distrust [8,9]. Language barriers, low health literacy, and cultural differences can also make it difficult for clinicians to adequately convey empathy and support [9–12]. Families of patients who die in intensive care units (ICUs) often suffer from anxiety and depression [13–16], post-traumatic stress disorder (PTSD) [14–16], and complicated grief [17], all of which can be exacerbated by social inequality [18–20]. Although it is recognized that EOL care in ICUs needs to be improved [21,22], no studies have evaluated palliative care interventions in the ICU in SNHs.

The 3 Wishes Project (3WP) improves the EOL experience by empowering healthcare workers (HCWs) and family members to elicit and fulfill modest wishes for critically ill patients who are dying in the hospital [23–25]. These small “wishes” are simply acts of kindness (often non-clinical) that are implemented to improve the patient’s and families’ EOL experience. Examples have included: playing the patient’s favorite music, providing the patient with a non-hospital blanket, allowing the patient to spend their final moment outdoors, giving the patient a taste of their favorite food or drink, decorating the room with the patient’s favorite memorabilia, and providing the bereaved family with keepsakes. The 3WP has been shown to enrich interpersonal connections among patients, family members and clinicians, ease family grief, and enhance clinician satisfaction [23–31]. The direct cost of wishes averages $30 per patient, and the 3WP has been shown to be acceptable and valuable to families, clinicians, and hospital leadership in a small sample of high-resourced hospitals [24,28,32]. However, data are lacking about strategies for successfully implementing 3WP in low-resourced hospitals, where patient’s experience of EOL and palliative care may be influenced by low health literacy, heterogeneous cultural perspectives, and limited English proficiency [33,34].

Because the 3WP has been shown to enhance clinician satisfaction, there is also potential for it to reduce burnout in HCWs, particularly nurses. The U.S. healthcare system is experiencing a critical shortage of nurses, and one of the most common reasons for the exodus of critical care nurses from their profession is burnout [35–37]. In our prior studies, 3WP was most frequently initiated and implemented by nurses (up to 75.7%) [24,38]. EOL care is one of the most emotionally and psychologically challenging aspects of bedside care [39–42]. As such, by providing structure and resources, and empowering SNH nurses to elicit and implement final wishes for dying patients and their families, the 3WP can potentially enhance the meaningfulness of work, decrease emotional isolation and depersonalization, and destigmatize the natural emotional responses to EOL care in the ICU [27].

We hypothesize that with the help of a tailored implementation strategy, which includes training materials and tools for bedside implementation and unit-level engagement, the 3WP can be implemented within the constraints of a resource-poor setting, improve nursing burnout, and improve the quality of EOL ICU care for dying SNH patients. In this paper, we describe a pragmatic type 2 hybrid effectiveness-implementation study (NIH R01NR020773), in which the 3WP is implemented using a cluster-randomized stepped-wedge study design at 3 SNHs. Using mixed methods, we will measure the effects of 3WP on two key clinical outcomes: a) the quality of EOL ICU care and bereaved families’ psychological symptoms, and b) nurse burnout as compared to usual care. We will also measure key implementation outcomes guided by the RE-AIM framework (Reach, Effectiveness, Adoption, Implementation, and Maintenance) [43] via quantitative measurement of reach and adoption as well as qualitative interviews with families and clinicians to measure additional implementation processes and outcomes. We hypothesize that the 3WP can be implemented in resource-poor settings and will improve the quality of EOL ICU care for dying patients and for nurses in SNHs.

## 2. Clinical intervention: The 3 Wishes Project (3WP)

The 3WP is a palliative care intervention in which clinicians, most commonly the patient’s bedside nurse, elicit and fulfill small wishes for critically ill patients who are dying in the ICU [23]. Our previous multi-center study in demonstrated the value, affordability, and sustainability of the 3WP at four tertiary academic centers in North America [24]. Examples of wishes include playing the patient’s favorite music, creating keepsakes for the family, and personalizing the environment with decorations and items from home [29]. The number and type of wishes depends on the needs of the patient/family, and an average of 3.4 wishes (range 1–10) were implemented per patient at an average cost of approximately $30 per patient.

## 3. Methods

### 3.1. Overview

Prior to implementing the 3WP intervention, we will refine the components of the implementation strategy (below) by engaging stakeholders at each SNH. We will then use a cluster-randomized stepped-wedge type 2 hybrid effectiveness-implementation design to implement the 3WP and assess its effectiveness in improving the EOL experience for SNH patients and their families. One week prior to intervention roll-out, we will conduct training sessions with ICU nurses that go over 3WP objectives, ways to introduce the 3WP to patients and families, and resources available. We will establish a tailored inventory of items that can be used in wish fulfillment based on prior experience and suggestions from each SNH. A research assistant at each SNH will assist with logistics, support nurses with wish implementation if needed, and collect data. Each SNH ICU (cluster) begins in the control phase and will start 3WP implementation at a randomly assigned time (wedge) (Fig 1). Implementation at each center will be staggered by 2 months. This design is useful in situations where 1) there is evidence of efficacy [23,24,26–30] and there is more potential for the intervention to do good than harm, 2) the traditional experimental randomization may be viewed as inappropriate given the nature of the intervention (a stepped-wedge design would allow all safety-net ICUs to initiate the 3WP), and 3) there are logistical constraints to randomization (3WP is a unit-level intervention and randomization at the patient level will likely result in contamination) [44,45].

**Fig 1 pone.0320843.g001:**

Stepped-wedge study design.

Each safety-net hospital will begin in the control phase and will implement the 3 Wishes Program at a randomly assigned time.

After 2.5 years, we will conclude survey collection and remove the research assistant who was available to assist with wish implementation. We will continue to provide monetary resources to purchase wish items and ask clinicians to continue documenting on 3WP during a 12-month maintenance period. Data on expenses and resource utilization will be collected during this period to provide hospital leadership with an estimation of 3WP cost when the detailed evaluation is complete and there is no on-site research assistant to facilitate this palliative care intervention. (IRB #23-0617).

### 3.2. Setting

The 3 SNHs in this study are part of the Los Angeles County Department of Health Services (DHS), which is the second largest municipal health system in the nation and provides care to patients regardless of their ability to pay. Over 50% of patients do not speak English and about 10% are unhoused. The patient population is 55–80% LatinX, 20% Asian, and 10% black, with many living individuals below the federal poverty level. Although all 3 hospitals serve poor, under- or uninsured, and non-English-speaking patients, they are of different sizes, have different geographical catchment areas, and patient populations. Because the mortality is the highest in medical ICU’s, this is where we will implement and evaluate the 3WP in these 3 Los Angeles DHS SNHs. Of note, hospital 1 only has one combined medical-surgical ICU.

### 3.3. Participants

To participate in the 3WP, a patient must be: 1) a critically ill adult in the ICU and 2) have a high risk of dying during the hospitalization as judged by the ICU physician, or a decision has been made to withdraw or withhold life support in anticipation of death. Family member(s) and/or the person listed as the patient’s designated decision maker (hereafter referred as family) can be included in wish solicitation and fulfillment. Based on our prior experience, we anticipate less than 10% of patients will be able to express their wishes due to critical illness [28,46]. Eligibility identification and wish solicitation and fulfillment are performed by any clinician, typically the ICU nurse and confirmed with the ICU physician(s). The 3WP is not meant to substitute a goals of care conversation, and as such, the nurse who wants to implement 3WP would confirm with the ICU physician that the patient is an appropriate candidate, and that the family is aware of their poor prognosis.

Regardless of whether the patient participates in the 3WP, families of all patients who die in the ICU will be contacted to complete an after-death survey. “Families” are those who are listed as the emergency contact or next of kin in the patient’s medical record, must be ≥ 18years old, and English- or Spanish-speaking. We anticipate that contact information will be missing for 5–10% of patients (i.e., due to homelessness). Additionally, families (10 per site) of patients who participated in the 3WP will also be invited for semi-structured interviews. All nurses (approximately 250 nurses across 3 ICUs) who work in the ICU in which the 3WP is being implemented will be eligible to complete surveys regarding burnout and compassion before and after 3WP implementation. Ten nurses at each site who have implemented the 3WP for their patients will also be invited to semi-structured interviews.

### 3.4. Implementation strategy refinement with stakeholder engagement

The 3WP implementation strategy is operationalized as having a series of core functions and customizable forms based on a conceptual model by Jolles et al. [47] (Table 1). In this framework, the core functions are the primary purposes that the implementation approach seeks to achieve, while the forms are the specific activities that can be customized with input from each SNH to operationalize the core functions. The core functions are: 1) methods for engagement and training; 2) tools for bedside 3WP implementation; 3) a method for documentation and tracking, and 4) tools to encourage unit-level engagement. Strategies to implement 3WP will be individualized for each SNH.

**Table 1 pone.0320843.t001:** The 3WP implementation function and form matrix.

	Core functions	Forms (examples only, to be tailored by SNH)
Tools for initial engagement and training	Familiarize clinicians with 3WP mission and goals Train clinicians with 3WP initiation and bedside implementation process Establish on-the-ground champions	PowerPoint presentation to introduce 3WP to ICU clinicians Teaching videos on how to offer 3WP to patients/families Recommendations to establish day and night shift nurse champions
Tools for bedside wish elicitation and fulfillment	Decrease burden of bedside implementation Ensure equitable 3WP offering Provide information to patients/families on the program Guide elicitation and implementation of wishes that personalize the patient’s death and create positive memories for family	Script for nurses on how to introduce the 3WP Badge buddies to delineate steps Announce eligible patients in daily multidisciplinary rounds or morning huddles List of inventory items (blankets, keepsake supplies, gift certificates to local stores, etc.) & recommendations to stock in accessible area 3WP informational brochures for patients/families Examples of possible wishes to suggest/implement
Tools to document and track	Communicate 3WP implementation with other members of the clinical team Track 3WP implementation (patients, families, and clinicians who participated, wishes achieved and cost)	Templates to assist with EHR documentation Online database to record patients who participated, the wishes fulfilled, and cost
Tools for unit-level engagement and recognition	Provide recognition and motivation for the team’s work Communicate progress and address questions and concerns	Templates for emails and flyers/posters summarizing accomplishments Guidance for conducting quarterly meetings to share stories and address questions and/or concerns

The forms listed in Table 1 are based on our prior experience but will be shaped by semi-structured interviews with stakeholders to best conform to the local needs and context of each hospital. Site lead investigators will identify key stakeholders at each SNH and semi-structured interviews will be conducted with 15–20 (5–7 per SNH) nurses and physicians during the pre-implementation phase. Interview questions are designed to identify actionable contextual factors using the Consolidated Framework for Implementation [48]. They address characteristics of the proposed implementation approach (usefulness of components, the need for additional forms or core functions), the optimal process (establishing 3WP champions, documenting participants and wishes, sharing 3WP achievements with the clinical team), the outer setting (SNH priorities, including concerns about new interventions and resource constraints), inner setting (ICU infrastructure, compatibility with workflow, space for 3WP inventory), and the characteristics of the individuals involved (diverse patient/family needs, nursing time constraints). At least 3 members of the research team will listen to interview recordings and independently perform content analysis [49,50] to identify all forms suggested by participants. The researchers will discuss findings and produce a complete core function/form matrix listing all suggested forms by core function.

### 3.5. Data collection

#### 3.5.1. Electronic health record (EHR) abstraction.

Each decedent will be characterized using EHR data, including the patient’s age, sex, race/ethnicity, language, insurance status, co-morbidities, and ICU and hospital length of stay. We will also note palliative care consultations, utilization of life-sustaining treatments (mechanical ventilation, vasopressors, or dialysis), and the occurrence of CPR as these factors have been shown to be associated with quality of death [51–53]. We will manually abstract occurrence of family meetings, reason for ICU admission, resuscitation status at the time death, whether the family was present at the time of death, and whether the death was expected. Expected death is defined as any physician documentation during the terminal hospitalization that the patient was terminal, had a grave prognosis, was receiving hospice care, had imminently life-threatening disease in the context of a poor prognosis, or was dying; this information was previously reliably abstracted from the medical record (reabstraction κ=0.67; 91% agreement) [54]. Double abstraction will be performed for 30 patients and a kappa will be calculated to evaluate inter-rater reliability, with appropriate changes in abstraction process or abstractor training implemented to increase inter-rater reliability if needed.

#### 3.5.2. Surveys.

An after-death survey that assesses perceptions regarding EOL care (Bereaved Family Survey (BFS)) [55] and psychological symptoms (Hospital Anxiety and Depression Scale (HADS) [56] and PTSD Checklist for DSM-5 (PCL-5) [57]) will be mailed to each family of an ICU decedent throughout the study period, 3 months after the patient’s death (both pre- and post-intervention) (Fig 1). The postal mailing will include a stamped return envelope, a phone number and email address for questions, and a letter stating that completing the survey implies consent and that there will be a $40 honorarium for completion. Surveys will be tracked using a unique code. Two weeks following the initial mailing, non-responders will be called up to 3 times (at least one attempt after 5pm and maximum two voice messages) to remind families to mail it back, or to complete it by phone or online. We are anticipating a return rate of approximately 40% based on our group’s prior experience [58,59] and other studies evaluating the quality of dying [60–62].

All nurses in participating ICUs will be invited to complete on-line surveys during the month prior to 3WP training and at 6 and 12 months after 3WP implementation. The survey will include the Maslach Burnout Inventory-Human Services Survey (MBI-HSS) [63] as well as questions regarding nurse’s age, sex, race/ethnicity, marital status, years of experience, average number of hours worked per week, and whether the nurse works day or night shift. Surveys will also ask nurses to rank 4 statements (0–4 scale) to assess the extent of implementation fidelity to core functions: 1) The introductory/training sessions provided me with the necessary instructions for 3WP implementation. 2) Available tools and materials made it easy to implement 3WP at the bedside. 3) I feel comfortable documenting 3WP implementation. 4) My ICU has embraced the 3WP as a unit-level intervention. There are approximately 250 ICU nurses across the 3 SNHs and we are anticipating 150 nurse evaluations at each time point (60% response rate). The survey will take 10–15 minutes to complete, will be compensated with a $20 gift card, and will include coded identifiers to link pre- and post-implementation surveys.

#### 3.5.3. Semi-structured interviews.

At each SNH, we will recruit 10–12 family members of patients who participated in the 3WP for semi-structured interviews (prior studies have shown that 92% of themes are identified in the first 10–12 interviews) [64,65]. Families will be contacted 10–12 weeks after the patient’s death. Interviews will be conducted in Spanish or English and will be audio-recorded. A semi-structured interview guide will be used to query family members about their experience with their loved one’s EOL care, the impact of the 3WP on their experience, any barriers/facilitators to participating in 3WP, and any influence of the 3WP on their grieving process and well-being. Interviewees will be verbally consented and receive $25 for their participation.

After 1 year of 3WP implementation, site PIs will recruit ICU nurses for interviews. Participants must have implemented the 3WP for at least one dying patient. Approximately 10–12 nurses will participate in semi-structured interviews at each SNH. Interview questions will explore whether and how the 3WP affected nurses’ sense of personal accomplishment, depersonalization, and emotional exhaustion in the care of dying patients. Interviewees will be verbally consented and receive $25 for their participation.

### 3.6. Outcomes and analysis

#### 3.6.1. Patient/family outcomes.

The primary outcome is changes in the Emotional and Spiritual Support factor on the family reported BFS after 3WP implementation. Three BFS-derived measures will be analyzed: Respectful Care and Communication (5 questions, Cronbach α = 0.82), Emotional and Spiritual Support (3 questions, Cronbach α = 0.77), and the BFS-Performance Measure (BFS-PM). The Respectful Care and Communication factor score sums 5 items about staff behavior: (1) listened to concerns; (2) provided medical treatment patient wanted; (3) were kind, caring, and respectful; (4) kept family members informed about patient’s condition and treatment; and (5) attended to personal care needs. The Emotional and Spiritual Support (ESS) factor score sums 3 items about whether staff provided: (1) enough emotional support before death; (2) enough spiritual support; and (3) enough emotional support after death. Based on our prior work [31], we hypothesize that the 3WP will increase the ESS factor score. The BFS-PM, a single item asking for a global rating of EOL care, will be a secondary outcome. Secondary outcomes will also include scores on the HADS (depression and anxiety) and PCL-5 (PTSD) measures.

**Statistical analysis**. We will use an analysis approach that accounts for the stepped-wedge design of this study [66,67]. We will use mixed effects logistic and linear mixed effects models to assess the effect of the intervention on the BFS ESS factor score, BFS-PM, FS-ICU, HADS, and PCL-5. These models adjust for center effect and the confounding effects of time and 3WP implementation. With $Y_{ijt}$ as the quantitative outcome for patient i from center j at time t, the model for patient/family reported outcomes is:

$Y_{ijt}=\mu +\alpha_{j}{\;+\;\beta }_{t}+X_{ijt}\theta +\;Z_{ijt}\varphi +\in_{ijt},$

where μ is the intercept, $\gamma_{i}$ is a random center effect,
$\beta_{t}$ is the fixed time effect, $X_{ijt}$ is the indicator of treatment mode for subject i cluster j at month t, θ represents the 3WP implementation effect, $Z_{ijt}$ are pre-specified patient and practice level covariates and $\in_{ijt}$ is random errors. We will also approximate the secular time trend $\beta_{t}$ linearly in time with βt. This model will accommodate unobserved center effects. All analyses will be carried out based on the intention to treat principle, which means that the treatment mode variable ($X_{ijt})$ is determined by the scheduled initiation of implementation based on randomization, but not by individual patient/family enrollment in the 3WP. Covariates, including age, sex, race/ethnicity, language, insurance status, and utilization of life-support measures, will be included in the model. We will also perform “as-treated” analyses to compare patients before implementation and patients who received 3WP after implementation and those who did not. Subgroup analyses will evaluate how outcomes are affected by race, ethnicity, and sex as a biological variable.

**Power calculations.** The primary outcome is the family-reported ESS factor score on the BFS, and the secondary endpoints include BFS-PM, FS-ICU, HADS and PCL-5. Across the 3 SNH ICUs, we estimate that 375 (90%) deaths per year will qualify for after-death surveys About 40% of families will return the survey based on our prior work [58,59]. With approximately 100 surveys returned before and 275 surveys after 3WP implementation and a 2-sided significance (α) level of 0.05, we will have 89.3% power to demonstrate the difference in the BFS ESS factor based on our preliminary data [59].

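### The primary model adjusts for life-support use, which is recorded after the intention-to-treat exposure with no time cut-off, so θ equals the total implementation effect only if 3WP leaves life-support use unchanged

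*Protocol article*

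**What the plan says.** Section 3.6.1 (Statistical analysis) gives a mixed model in which θ is the effect of 3WP implementation. Treatment mode "is determined by the scheduled initiation of implementation based on randomization, but not by individual patient/family enrollment in the 3WP". The covariates are age, sex, race/ethnicity, language, insurance status and, last in the list, life support: "utilization of life-support measures, will be included in the model".

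Section 3.5.1 shows where that covariate comes from. For each decedent the record is abstracted for "utilization of life-sustaining treatments (mechanical ventilation, vasopressors, or dialysis"), among other items, because "these factors have been shown to be associated with quality of death". Comorbidities and the reason for ICU admission are abstracted as well. No time window is attached to life-support use.

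Section 3.3 gives two routes into 3WP, joined by "or" in the text: the ICU physician judges that the patient is likely to die during the stay, or "a decision has been made to withdraw or withhold life support in anticipation of death". It adds that "The 3WP is not meant to substitute a goals of care conversation".

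**The concern.** An intention-to-treat effect defined by launch date is the total effect of introducing 3WP in the unit, by whatever route it acts. A covariate that the programme cannot alter, such as age or insurance, leaves that effect intact. Life-support use is different: it reflects treatment decisions made during the stay, and for anyone admitted after launch the stay lies wholly inside the exposed period.

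If launching 3WP shifts how often these treatments are used, and use is related to the family's rating, the covariate lies on the path from exposure to outcome. Conditioning on it then removes that part of the effect. It can also link exposure with any unmeasured severity that drives both life support and the rating. What is at stake is the meaning of the primary estimate: θ would be a partly direct effect reported as the implementation effect.

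**Working it through.** **Step 1. Timing, from the text.**

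| Element | What the article fixes | Section |
|---|---|---|
| Exposure | The ICU's scheduled launch, regardless of enrolment | 3.6.1 |
| Covariate | Ventilation, vasopressors or dialysis, per decedent, no cut-off stated | 3.5.1, 3.6.1 |
| Earliest 3WP contact | Possible once the physician judges death likely, hence before any decision to withdraw or withhold | 3.3 |
| Link to outcome | Stated association with quality of death, direction and size not given | 3.5.1 |

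The covariate is post-exposure for patients admitted after launch. A path from 3WP to life-support use is possible through the first eligibility route, but it is not documented.

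**Step 2. The scale of the planned effect.** Section 3.6.1 gives 100 surveys before launch, 275 after, two-sided α of 0.05 and 89.3% power. It gives neither the difference nor the SD, so the power cannot be reproduced forwards. Solving backwards with a two-sample normal approximation:

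- standard error = √(1/100 + 1/275) = 0.117 SD
- implied d = (1.960 + 1.243) × 0.1168 = 0.374 SD
- entering d = 0.374 returns 89.3%.

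This ignores clustering and the time effect.

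**Step 3. What adjustment would remove.** Let *a* be the change in life-support prevalence caused by 3WP and *b* the association of life-support use with ESS in SD units. The part removed is a × b. Neither value is in the article; those below are assumptions, taken to act in the same direction, so that adjustment shrinks the effect. With opposite directions it would enlarge it.

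| Assumed shift | Assumed association | Removed (SD) | Share of 0.374 | Remaining d | Power |
|---|---|---|---|---|---|
| 0 points | any | 0 | 0% | 0.374 | 89.3% |
| 5 points | 0.2 | 0.05 × 0.2 = 0.01 | 2.7% | 0.364 | 87.6% |
| 10 points | 0.3 | 0.10 × 0.3 = 0.03 | 8.0% | 0.344 | 83.8% |
| 15 points | 0.4 | 0.15 × 0.4 = 0.06 | 16.0% | 0.314 | 76.7% |

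The power column also ignores any precision gained from the covariate.

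**Step 4. Shared severity.** A simulation of 2,000,000 records per setting used a true total effect of 0.374 SD, 275/375 of records exposed, life-support prevalence of about 70% and b of 0.3 SD (use lowers ESS, 3WP lowers use). It was run without and with an unmeasured severity factor that raises life-support use by 15 points and lowers ESS by 0.3 SD per SD of severity. Ratio of adjusted to unadjusted effect:

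| Assumed shift | No shared severity | Shared severity |
|---|---|---|
| 0 points | 0.999 | 0.999 |
| 5 points | 0.96 | 0.93 |
| 10 points | 0.92 | 0.87 |
| 20 points | 0.84 | 0.74 |

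With no shift there is no bias, even with shared severity. With a shift, shared severity increases the loss.

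**The case against.** The strongest reply is that nothing in the article says 3WP alters organ support. The wishes are described as "acts of kindness (often non-clinical") and act on emotional support directly. On one eligibility route the decision to withdraw or withhold comes before 3WP, and the programme does not replace the goals-of-care conversation. If the covariate is coded as ever used, later withdrawal cannot change it, and much of it will predate a patient's own contact with 3WP. All of this stands, and it makes zero shift a serious possibility. It does not close the path, because the other route allows 3WP while life support may still be started.

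A second reply is that life-support use is the closest marker of acute severity among the abstracted items. With three ICUs and about 40% survey return, responding families may differ in case-mix before and after launch. This also stands, as a reason to show the adjusted model, but not as a reason to make the primary effect rest on an untested assumption.

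Third, coding and timing may be defined in a fuller protocol or SAP. That is possible, and an admission-based definition there would meet the point. As published, though, the article names the covariate for the model, which is a stated choice rather than a detail left open.

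Finally, even 0.06 SD is only about half of one standard error (0.06/0.117 = 0.51).

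**Conclusion.** The point holds in conditional form. The primary model adjusts for a treatment variable recorded after the exposure, with no cut-off, so θ is the total implementation effect only if 3WP does not change life-support use. Under the assumptions shown, the loss runs from nothing to 0.06 SD, or 0 to 16% of the implied 0.374 SD, and is larger if unmeasured severity drives both life support and ESS. None of these shifts or associations comes from the article, and the 0.374 SD is itself back-solved.

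Three stronger readings are tempting and are not supported:

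- A reader might infer that part of the effect is certainly adjusted away. No section reports or implies a change in life-support use.
- A reader might infer that the bias would be inseparable from a real difference. Life-support use is abstracted for every decedent in both periods, so its shift can be inspected and the model refitted without it.
- A reader might take the covariate to be defined over the whole terminal hospitalization. In section 3.5.1 that phrase belongs to the definition of expected death; for life-support use the window is simply not stated.

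This is a low-cost improvement to the primary analysis rather than a fatal flaw.

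**What to change.** In section 3.6.1, make the model without life-support use primary, keeping age, sex, race/ethnicity, language and insurance status, and adding the already abstracted comorbidities and reason for ICU admission for case-mix. Alternatively, keep the covariate but restrict it to a value fixed at ICU admission, before possible 3WP contact. Report the life-support-adjusted model as a sensitivity analysis, together with life-support use before and after launch, so that readers can see whether it moved and whether the choice of model matters.

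The cost is a sentence or two of text and no new data. There may be a small loss of precision, and some adjustment for acute severity is given up in the primary model. Section 3.7 expects survey collection to run to about June 2027 and results in 2028, so the change can be recorded before analysis.
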